### Outcomes

The primary outcomes will be the differences between the intervention and control groups with regard to changes in dietary habits, knowledge and physical activity of the participants, from the beginning to the end of follow-up for children and adults. The secondary outcomes will be the differences between the intervention and changes in body mass index, waist circumference, systolic and diastolic blood pressure, total cholesterol, LDL-cholesterol, HDL-cholesterol, triglycerides, glucose, complete blood count and C-reactive protein, both in children and their parents. Figure 2 presents a timeline for assessing the outcomes.

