**Study timeline for intervention and assessment of outcomes.**

### Evaluation of outcomes

Time schedules for both groups is presented in Figure 2. All results will be evaluated at the beginning and at the end of follow-up, in all participants in the intervention and control groups.

A general evaluation questionnaire will be administered to the parents, to identify personal details of parents and children, breastfeeding time, age of introduction of complementary foods, early and family history. Evaluation tools used with the children will include the “TDPA” and the “Cardiokid” questionnaires.

The TDPA (Typical day of physical activity questionnaire) is an illustrated and structured questionnaire, developed in the Portuguese language by a group of researchers from Brazil, with the purpose of obtaining information about a typical day of physical activity [41]. The questionnaire was developed for children aged 7 10 years and is evaluated by a sum of scores: children reaching a total lower than 36 classified as “less active”, from 37 to 58 as “intermediate”, and from 59 to 141 classified as “most active” [41].

The Cardiokid questionnaire was developed in the portuguese language with the aim of evaluating knowledge about healthy habits and risk factors for cardiovascular disease [42]. It presents 12 illustrated and colourful questions, with three alternative answers represented by faces: “smiling” (good for the heart), “sad” (bad for the heart) and “neutral” (I don’t know). The sum of right answers determines the level of knowledge: “excellent knowledge” (11 to 12), “good knowledge” (eight to 10) and “insufficient knowledge” (below seven correct answers) [42].

The blood pressure will be measured with the appropriate size cuff. Three readings, each about two minutes apart, will be taken on the right arm, in a sitting position, with the arm supported at heart level, after a 10 minutes rest. The average of the last two measurements will be used for the analysis. For children, the systemic blood pressure will be considered abnormal if the systolic and/or diastolic measurement is greater than or equal to the 95th percentile for gender, age and height percentile [42-45]. For adults, values of systolic blood pressure ≥ 140 mmHg and/or diastolic blood pressure ≥ 90 mmHg [46] will be considered abnormal.

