### Sample size

Sample size was estimated considering a possible reduction of 20 g/dL and standard deviaton of 29,9 on total cholesterol in the intervention groups, similar to the observed in another Brazilian study [53]. The sample size was thus estimated as 37 patients in each group, considering a significance level of 0,05 and power of 0,80, with the aid of an online sample size calculator (Russ Lenth) USA [54]. Considering the outcome “BMI change”, to detect a standardized difference of 1,0 as observed by “Effects of a School-based Weight Maintenance Program for Mexican-American Children: Results at 2 years, with a bilateral alpha of 0,05 and power of 0,8, we estimated the need of a sample size of 17 participants per group [55].

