### Data analysis

Data will be analyzed according to the intention-to-treat approach, with the Statistical Package for the Social Sciences (SPSS) version 20.0. Continuous variables will be expressed as means and standard deviations, and categorical variables, in absolute and relative frequencies. Groups will be compared with the Student’s *t* test for continuous variables and Chi-square test for categorical variables. Analysis of variance (ANOVA) for repeated measures will be used for intra and inter-group comparisons. Since this is a short duration trial and risks are considered minimal, we do not plan to perform interim analysis. The significance level adopted will be 5%.

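### Comparing arms by t test and repeated-measures ANOVA, without conditioning on baseline, is valid but less precise than ANCOVA, and the planned within-arm tests are not treatment comparisons

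*Protocol article*

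**What the plan says.** The Outcomes section defines a between-arm comparison of change: "The primary outcomes will be the differences between the intervention and control groups with regard to changes in dietary habits, knowledge and physical activity". The Evaluation of outcomes section fixes two measurement times: "All results will be evaluated at the beginning and at the end of follow-up, in all participants in the intervention and control groups". The Study design section places the initial assessment before randomisation.

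The Data analysis section compares the groups with Student's t "test for continuous variables and Chi-square test for categorical variables". It then adds: "Analysis of variance (ANOVA) for repeated measures will be used for intra and inter-group comparisons". It does not say whether the t test is applied to final values or to changes. It does not say which of the two methods decides, and it names no baseline covariate. Within-arm comparisons are listed beside between-arm ones, with nothing to mark them as descriptive.

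**The concern.** A baseline value is collected for every outcome, but neither named method uses it as a covariate. A t test on final values ignores baseline. A change-score test, or the equivalent group-by-time term, subtracts the whole baseline value whatever its correlation with the end value. ANCOVA estimates how much to subtract, so its large-sample variance is never higher than either. In a trial of 74 children, precision is given up although the data to recover it are already in hand.

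The second issue is the within-arm tests. A p-value for change inside one arm says nothing about the difference between arms. Controls are also actively managed, with visits every two weeks, a booklet and individual targets, so change in both arms is plausible. If one arm's change is significant and the other's is not, that pattern could be reported as an effect of the programme when the arms do not differ.

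**Working it through.** **Inputs from the Sample size section.** Difference and SD: "considering a possible reduction of 20 g/dL and standard deviaton of 29,9 on total cholesterol in the intervention groups". Size: "estimated as 37 patients in each group, considering a significance level of 0,05 and power of 0,80". The article does not say whether 29.9 is the SD at one time or the SD of change. It gives no baseline-to-end correlation r, so r is assumed over 0.3 to 0.9.

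**Reproducing the plan's own figure.** Standardised effect = 20/29.9 = 0.67. A two-sided two-sample t test at 5% with 80% power needs 37 per group (exact noncentral t; 36 by the normal approximation), and power at 37 is 0.81. A one-sided test would need only 28 or 29. The stated size is therefore that of an unadjusted two-sided t test.

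**Variance formulas.** Let s be the single-time SD, equal at both times and in both arms:
- t test on final values: s²
- t test on change, identical to the group-by-time test with two time points: 2s²(1 − r)
- ANCOVA on baseline: s²(1 − r²)

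Hence ANCOVA/change = (1 − r²)/[2(1 − r)] = (1 + r)/2, and ANCOVA/final = 1 − r².

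| r (assumed) | ANCOVA/change | ANCOVA/final |
|---|---|---|
| 0.3 | 0.65 | 0.91 |
| 0.5 | 0.75 | 0.75 |
| 0.7 | 0.85 | 0.51 |
| 0.9 | 0.95 | 0.19 |

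**Power at 37 per arm, difference 20, 29.9 taken as the single-time SD.**

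| r | Final value | Change | ANCOVA |
|---|---|---|---|
| 0.3 | 0.81 | 0.67 | 0.85 |
| 0.5 | 0.81 | 0.81 | 0.91 |
| 0.7 | 0.81 | 0.96 | 0.98 |

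For example, at r = 0.5 the ANCOVA residual SD is 29.9 × √0.75 = 25.9, against 29.9 for both alternatives. At r = 0.7 it is 29.9 × √0.51 = 21.4, against 29.9 × √0.6 = 23.2 for change. These figures ignore the one degree of freedom spent on the covariate. A simulation with 10,000 trials at each of r = 0.5 and 0.7, which does spend it, gave ANCOVA power of 0.91 and 0.98.

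**If 29.9 is instead the SD of change.** The change test keeps power 0.81 at every r. ANCOVA has residual SD 29.9 × √[(1 + r)/2] and power 0.91, 0.87 and 0.83 at r = 0.5, 0.7 and 0.9.

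**Within-arm tests.** Suppose both arms truly change by the same amount. Let p be the chance that one arm of 37 reaches p < 0.05 on a paired t test. The chance that exactly one of the two arms does so is 2p(1 − p).

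| Common change (in SDs of change) | p | Exactly one arm significant |
|---|---|---|
| 0 | 0.05 | 0.10 |
| 0.2 | 0.22 | 0.34 |
| 0.33 | 0.50 | 0.50 |
| 0.5 | 0.84 | 0.27 |

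**The case against.** The strongest defence is that nothing here is invalid. With two time points, the group-by-time term of the repeated-measures ANOVA is the t test on change. It uses the baseline, is unbiased under randomisation, and targets the quantity that the Outcomes section makes primary. If that term decides and r is high, the gain from ANCOVA is small: 5% of variance at r = 0.9, and two points of power at r = 0.7 in the cholesterol example. All of this stands, and it limits the point to precision and to the status of the within-arm tests. It does not remove the point, because the Data analysis section states its methods and ANCOVA does at least as well at no cost.

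A reader might infer more than the article supports:

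- **That the between-arm result will be read from the ANOVA group main effect, which averages baseline with follow-up.** The Data analysis wording is loose, but it does not say this, and the Outcomes section points to the group-by-time term.
- **That the plan contradicts its own intention-to-treat statement.** The article says: "Data will be analyzed according to the intention-to-treat approach, with the Statistical Package for the Social Sciences (SPSS) version 20.0". Repeated-measures ANOVA run without imputation would omit a child lacking the final value. Nothing in the article says that such children will be dropped, and missing-data handling is commonly left to a fuller document.
- **That regression to the mean will distort the primary outcomes.** Children enter on weight, blood pressure, lipids or diabetes. Dietary habits, knowledge and physical activity are not entry criteria. Regression to the mean therefore concerns the children's secondary risk-factor outcomes, and there it affects both arms alike and leaves the between-arm contrast unbiased.

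**Conclusion.** The point holds as a free improvement, not as an error that undermines the trial. The planned between-arm comparison is unbiased but less precise than ANCOVA. The variance ratio against the change-score test is (1 + r)/2, and against a t test on final values it is 1 − r². At the article's own effect, the gain in power at r = 0.5 is about 10 points over either alternative. At r = 0.7 it is about 2 points over change and 17 over final values.

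These sizes rest on an assumed r, on equal SDs at both times, and on reading 29.9 as a single-time SD. If it is the SD of change, the gain is about 10, 6 and 2 points at r = 0.5, 0.7 and 0.9. Total cholesterol is a secondary outcome, and the Sample size section gives no effect size for the primary ones. The variance ratios carry over to those scores at whatever r they have; the power figures do not.

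The within-arm tests should not support conclusions about the programme. With equal true change in both arms, exactly one arm can be significant in up to about half of trials. The between-arm definition of the primary outcomes gives some protection, but the Data analysis section does not carry it through.

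The sample size is not at fault on this point: 37 per group reproduces, and ANCOVA would add power at that size.

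**What to change.** In the Data analysis section, state that for each continuous outcome the deciding analysis is an ANCOVA of the end-of-follow-up value on arm, with that outcome's baseline value as covariate. Report the adjusted between-arm difference with its 95% confidence interval. Report within-arm changes as means and SDs, without p-values, and base conclusions about the programme only on the between-arm difference.

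The cost is a change of wording. Baseline is already measured in every participant before randomisation, the named software fits the model, one degree of freedom is spent, and neither recruitment nor assessments change.

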### Project timelines

The recruitment of the participants began on October 1, 2013. Analyses are expected to be completed, with discussion of the first results, in March 2014.

### Ethics and divulgation

#### Ethics

In order to comply with the ethical issues in research, the project was submitted to the Research Ethics Committee of Institute of Cardiology – Fundação Universitaria de Cardiologia.

All participants will sign an informed consent form, in accordance to well-established practices. For that, they will be informed about the objectives of the study, and any questions will be answered by the researcher. All participants will be able to discontinue participation at any time, without the need for any explanation. The data will be under the guard of the researcher, with secrecy and confidentiality guaranteed.

After analysis, the data collected will be archived by the researcher for at least five years, and then will be destroyed by tearing and burning. At the end of the study, a final report will be sent to Instituto de Cardiologia, where it will be accessible to the participants of the program. A manuscript will be prepared for publication in scientific journals.

#### Divulgation

The results of this study will be widely publicized by presentations in lectures and by publications, aiming to contribute to improving child health in developing countries.

## Discussion

Although the vast majority of deaths attributed to cardiovascular diseases and obesity occur in adulthood, there is growing evidence that risks for these diseases begin in childhood and continue throughout life. In this context, early childhood education and care represents an special opportunity for prevention. Small changes in risk factors can have a considerable impact in improving the quality of life of the population.

The knowledge, attitudes, behaviors and skills developed through effective health programs may result in a better quality of life and empower children to make correct choices to promote the health of the individual, the family and the community [11,57]. To motivate participants and improve their adherence to these programs, some authors suggest the use of text messages (SMS) or phone calls prior to scheduled meetings [58,59]. Another important point to be considered is the relationship between health professionals and patients that help to ensure the adherence of patients to the proposals and guidelines [58-60]. The establishment of a relationship between patient and the professional team is important in helping the process of change, the awareness and capacity of resilience, even in the adoption of a new lifestyle [59,60].

Various methods are used to improve habits of children; however, studies show that educational alternatives, with recreational intervention strategies, are more efficient [44,61,62]. Recreational resources should be encouraged as supporting actors in the process, since during play the child acquires experience and knowledge, concepts and values. Playful activities, including games and toys, are effective instruments that facilitate the learning process, improving the child’s performance [63]. An innovative, low-cost protocol that can be easily applied in educational interventions for the treatment and prevention of cardiovascular diseases, using resources appropriate for the age group, can be used in multiple contexts [61,62].

The Happy Heart Study offers a playful and differentiated approach for the prevention and control of obesity and cardiovascular disease in children. Although this program is being planned for implementation in Brazil, the method can be adapted to many other countries. In developing countries, it is even more important to learn to prevent instead of dealing with the consequences of an established epidemics, and prevention depends on the implementation of health educational programs and healthy living habits.

Children are capable of quickly internalize what they learn, establishing a healthy lifestyle. They are also very able to spread this practice to the familiar context and to the society, as a whole increasing both short and long term results of preventive public health programs. The inclusion of the family in the intervention procedures was due to evidence that children’s treatment programs in which several members of the family participate are more successful than programs consisting only of food restriction. In addition, educational materials in the form of manuals will be provided for parents in some of the meetings.

The present protocol for prevention of chronic diseases is a simple and low cost tool, and can be incorporated into the school curriculum, in the community and in different contexts. It has the potential to produce beneficial health effects and thus considerably reduce public spending with health problems triggered in adulthood by overweight and physical inactivity in childhood, representing an important prevention strategy.
